## Abstract

**Background:**

Research has shown that improving well-being using positive mental health interventions can be useful for predicting and preventing mental illness. Implementing online interventions may be an effective way to reach young people, given their familiarity with technology.

**Objective:**

This study will assess the effectiveness of a website called the “Online Wellbeing Centre (OWC),” designed for the support and improvement of mental health and well-being in young Australians aged between 16 and 25 years. As the active component of the study, the OWC will introduce a self-guided app recommendation service called “The Toolbox: The best apps for your brain and body” developed by ReachOut.com. The Toolbox is a responsive website that serves as a personalized, ongoing recommendation service for technology-based tools and apps to improve well-being. It allows users to personalize their experience according to their individual needs.

**Methods:**

This study will be a two-arm, randomized controlled trial following a wait-list control design. The primary outcome will be changes in psychological well-being measured by the Mental Health Continuum Short Form. The secondary outcomes will be drawn from a subsample of participants and will include depression scores measured by the Center for Epidemiologic Studies Depression Scale, and quality of life measured by the Assessment of Quality of Life-four dimensions (AQOL-4D) index. Cost-effectiveness analysis will be conducted based on a primary outcome of cost per unique visit to the OWC. Utility-based outcomes will also be incorporated into the analysis allowing a secondary outcome to be cost per quality-adjusted life year gained (based on the AQOL-4D values). Resource use associated with both the intervention and control groups will be collected using a customized questionnaire. Online- and community-based recruitment strategies will be implemented, and the effectiveness of each approach will be analyzed. Participants will be recruited from the general Australian population and randomized online. The trial will last for 4 weeks.

**Results:**

Small but clinically significant increases in well-being symptoms are expected to be detected in the intervention group compared with the control group.

**Conclusions:**

If this intervention proves to be effective, it will have an impact on the future design and implementation of online-based well-being interventions as a valid and cost-effective way to support mental health clinical treatment. Findings regarding recruitment effectiveness will also contribute to developing better ways to engage this population in research.

**ClinicalTrial:**

This study is registered in the Australian New Zealand Clinical Trials Registry (ANZCTR): ACTRN12614000710628.

## Introduction

### Background

Positive mental health implies more than just the absence of illness, it relates to *positive symptoms* and emphasizes psychological, social, and generative dimensions such as positive affect, personal growth, social actualization, and social contribution among others [1,2]. Despite controversies surrounding the role of well-being in mental health, the concept of positive mental health is steadily gaining credibility [1]. There is evidence that people with high levels of positive mental health are physically healthier, live longer, are more productive at work, and use less health care [3].

Consistent with this reasoning, the World Health Organization defines mental health as “a state of well-being in which the individual realizes his or her own abilities, can cope with the normal stresses of life, can work productively and fruitfully, and is able to make a contribution to his or her community” [4]. Promoting positive mental health can be an effective strategy to approach mental health comprehensively as it is recognized that “the alleviation of symptoms of illness does not guarantee the presence of wellness” [5]. The Complete State Model of Mental Health characterizes mental health into three stages, namely, flourishing, languishing, or moderately mentally healthy, based on symptoms of positive feeling and functioning in life [6]. Keyes and Lopez [6] have posited that positive mental health constitutes a different continuum to mental illness and although correlated, the absence of mental illness does not imply the presence of positive symptoms [1]. Keyes [3] found that people with diagnoses less than flourishing struggled as much as people with a mental illness in areas such as work, health limitations, and psychosocial functioning [1]. In addition, the absence of positive mental health is associated with an increase in risky behaviors and the potential onset of mental illness [7]. A study conducted in South Australia reported that less than half of South Australian young people (42%) aged 13-17 years had a *flourishing* diagnosis of mental health, with even lower rates reported in rural areas [7]. This means that at the time of the study, 58% of young people in South Australia had less than a complete state of mental health (flourishing), and might therefore be more vulnerable to struggle in one or more areas of their lives.

### Online Well-Being Interventions

There is evidence that young people make significant use of the Internet to socialize and to find information about a wide range of issues including personal difficulties. In Australia, surveys show that the Internet is the preferred medium of support for young people after family and friends [8,9]. Specialized online mental health services for young people such as ReachOut.com have effective reach into this population group [10].

Online treatments based on a psychopathology model for a range of mental disorders such as depression and anxiety have been researched widely [11-14]. Most of these interventions are based on cognitive behavioral therapy (CBT) with specific variations such as prolonged exposure or guided relaxation, among others. These interventions have shown effectiveness in treating problems such as stress, anxiety, and depression. Other types of interventions such as general counseling and self-help approaches still show effectiveness, although to a lesser extent [11,12]

Regarding online positive psychological interventions, a number of studies in adult populations have shown positive results in improving well-being and decreasing depression. Results vary depending on the actual intervention and method of delivery [15]. Two recent trials with similar characteristics to this study demonstrated significant improvements in well-being in the general adult population, predominantly in women. Bolier et al [16] examined the effectiveness of an online self-help intervention consisting of a multicomponent, fully automated self-help online website to improve well-being. Their study investigated mild to moderately depressed adults in the general population using a waitlist control design, and found the online intervention to be effective in enhancing well-being on the 5-item World Health Organization well-being index [17] compared with a control. Small but significant effects were found for general health, vitality, anxiety, and depressive symptoms. Another study comprising a randomized, placebo-controlled, parallel-group trial with longitudinal outcome measurements used the Individual-level Wellbeing Assessment and Scoring Method to measure well-being [18]. It was found that a multimodal online intervention consisting of well-being e-mail, web- and mobile-based interventions had positive effects, with significantly improved well-being in a sample of the general adult population compared with a control.

There is a paucity of research on online positive mental health interventions in young people; however, a randomized controlled trial [19] investigated the effectiveness of a well-being website called “Bite Back” designed for young people aged 12-18 years. Using the Depression, Anxiety and Stress Scale (DASS21)[20] and the Short Warwick Edinburgh Mental Wellbeing Scale [21], the study participants were assigned to two conditions over a 6-week period. The intervention group was given access to the website and the control group was assigned to neutral entertainment-based websites. Results demonstrated significant improvement in clinical measures (depression, anxiety, and stress) and well-being in the participants of the intervention group who reported using the website for at least 30 minutes every week.

### Online Recruitment and Engagement

Facebook, Google, and other online platforms, frequented by large number of users, have been used widely with considerable success to recruit participants for online studies [22-24]. Both Google and Facebook advertising platforms have been effective in recruiting participants with an existing mental health issue for online interventions. The average cost of recruitment is approximately AUD 12-15 for each participant, whereas contacting forums, email groups, and community notice boards are less effective and more costly [24,25]. Although social networking websites can be a promising method to recruit adolescents, the health and behavior patterns of those recruited online could differ significantly from those recruited offline [22]. The evidence for effective strategies to recruit young people for online well-being interventions is sparse. Despite the proven efficacy of Internet-based mental health interventions, they suffer from a high reuse attrition rate [26]. In fact, findings from an online smoking cessation study with a high reach showed that adherence and retention rates decrease as accessibility increases [27]. Improving adherence is a high-priority research area in Internet interventions, as higher usage rates are associated with significant improvements in well-being [19]. Periodic prompts through email, short message service (SMS) text messaging, phone, and online peers/counsellors have proven to be effective strategies in increasing login rates and the time users spend using online interventions [28].

Research has shown that in the first few weeks after engagement with a given intervention, high numbers of participants lose interest [29]. Involving users in the intervention design process can be an effective way to create person-centered innovations [30]. Participatory design is characterized by generative, experiential, and action-based methods that put emphasis on play, co-operative learning, creating visions for the future, and designing-by-doing, with the aim of involving end users in the design of services [31]. Online studies that provide useful feedback and alternative resources for the control group achieve better engagement [18].

### Current Study

This study is a waitlist randomized controlled trial (ACTRN12614000710628) intended to test the effectiveness of an online intervention in improving well-being in a sample of Australian young people aged 16-25 years.

This paper provides a brief description about the Online Wellbeing Centre (OWC), outlining two different configurations for the implementation of interventions and how they were developed. It also includes a description of the methods, design of the trial, and finally a discussion with implications of this study.

## Methods

### Online Wellbeing Centre

The OWC was designed as a way to encourage individuals to participate in both intervention and control arms. The OWC is a virtual space where users sign up via the landing page (Figure 1), check their well-being, track their progress over time, and access different well-being resources. It has capabilities to randomize, administer study measures at different time points, and give access to tailored resources according to the assigned arms of the study. The OWC provides feedback to users in a meaningful graphic display as shown in Figure 2.

**Figure 1 figure1:**
[figure not shown]
Screenshot of the Online Wellbeing Centre landing page.

**Figure 2 figure2:**
[figure not shown]
Screenshots of the Online Wellbeing Centre website.

### Intervention arm: “The Toolbox” by ReachOut.com

The Toolbox has been developed by ReachOut.com, with the Young and Well Cooperative Research Centre (Young and Well CRC). It houses over 50 mental health and well-being tools and apps that have been reviewed by a panel of both mental health professionals and consumers for their credibility, functionality, engagement, and aesthetics according to the Mobile Application Rating Scale developed by Queensland University of Technology [32].

The Toolbox is based on the theory of change proposed by Perugini and Bagozzi’s Model of Goal-Directed Behaviour [33] as well as theories of reasoned and planned behavior [34]. The Toolbox focuses on well-being and positive functioning, and is designed to improve (1) emotional well-being (ie, positive affect and life satisfaction); (2) psychological well-being (ie, self-acceptance, personal growth, purpose in life, environmental mastery, autonomy and positive relations with others); (3) social well-being (ie, social acceptance, social contribution, social coherence, social integration, and social actualization); and (4) physical well-being [35]. In designing The Toolbox, ReachOut.com took a participatory design approach [31]. Young people were consulted at the initiation of the project and during the design phase, while also providing feedback on early prototypes. The user experience of The Toolbox is based on young people’s conceptualization of well-being and what they need from an online recommendation service. Functionalities of The Toolbox website are described in Textbox 1, and screenshots of the first 2 pages of The Toolbox website are shown in Figure 3.

Functionalities of The Toolbox.Quiz to help participants determine their area of focus and recommend relevant apps.Browse apps by category. Categories include Health & Fitness, Being Independent, Relationships & Helping Others, Thoughts & Emotions, and Dealing with Tough Times.Read ratings and reviews by health professionals and young people. Participants can write their own review of apps including what they liked and what could be improved.Read stories about how others have used apps to achieve their goals and the challenges they faced. Participants can submit their own story.Dashboards are available in which participants can update their goals, add new apps, and view their stories.

**Figure 3 figure3:**
[figure not shown]
The Toolbox website home page and app recommendation page.

### Study Design

This is a standard parallel arm clinical trial comparing the effectiveness and cost effectiveness of control and intervention arms offered over 4 weeks. Group 1 represents the intervention arm (OWC with The Toolbox) and Group 2 represents the waitlist control arm (OWC without The Toolbox). In this study, participants in the intervention arm will be able to access the active component of the trial, The Toolbox, through the OWC straight away. Participants in the control group will gain access to The Toolbox after 4 weeks. Once participants follow the online links as described in the recruitment section, they will be directed to the project’s landing page (Figure 1). Once there, they will be required to complete the steps outlined in Figure 4.

All participants will receive regular SMS and email prompts from the OWC to remind them to complete study measures. As detailed in Table 1, assessments will be administered at sign up, and at 4 weeks. In addition, participants will be prompted to regularly monitor their mood, energy and sleep.

**Table 1 table1:** Assessment scales administered at each time point during the study.

Instrument	Measurement	Baseline	After 4 Wk
Mental Health Continuum Short Form	Well-being/Positive mental health	X	X
Center for Epidemiologic Studies Depression Scale	Symptoms of depression	X	X
Assessment of Quality of Life-four dimensions index	Quality of life data	X	X
Resource use questionnaire	Cost effectiveness		X
Demographics	Date of birth, gender, postcode, employment, education, cultural background, and living conditions	X	
Heuristic well-being questions	Feelings, energy, and sleep	Weekly	Weekly

**Figure 4 figure4:**
[figure not shown]
Online Wellbeing Centre study flow diagram.

### Recruitment, Inclusion, and Exclusion Criteria

The target population is Australian young people aged between 16 and 25 years, with access to technology and the Internet (computers or smartphones). In the context of well-being theory, pre-existing mental health problems will not be considered as exclusion conditions for this study. Given that this intervention is not intended to treat any particular pathology, all participants could potentially benefit from improving well-being symptoms. Relevant links to appropriate mental health services will be offered to participants during the trial. Online recruitment will only be targeted to participants between 18 and 25 years of age. Parental consent will be obtained for participants under the age of 18 recruited via community channels, given that we will have face-to-face contact with potential participants through schools and other organizations. People not meeting the age criteria and/or residing outside of Australia will be excluded.

Participants will be recruited using online- and community-based methods. Two platforms have been selected from the many options available to implement online paid advertising. Advertisements will be placed on Facebook and Google AdWords (see Figure 5) using keywords relevant to well-being dimensions. The keywords for the advertisements were defined in collaboration with a reference group representing the target population to ensure their validity and relevance. Examples of such keywords include *fitness*, *stress*, *relationships*, *balance*, and *goals*. Concurrently, the links to the study site will be integrated into several websites that are frequently visited by young people from different backgrounds in Australia (most notably the partner organizations of the Young and Well CRC).

The online recruitment strategy also includes changing advertisements periodically. This will be a dynamic process guided and modified by success rates of particular advertisements while they are being implemented. The wording of the advertisements and placement of links will be monitored (according to the method described in the “Recruitment Tracking” section) and periodically modified to reach the target population effectively.

Community-based organizations such as schools, universities, sport clubs, and local councils will be approached and asked to help promote the study. Promotional packages consisting of a video, information, and instructions on how to access the OWC will also be designed. These packages will be distributed to different institutions where they will be presented to potential participants. Innovative technologies (videos, Google Hangouts, etc) will be included in the recruitment packages.

**Figure 5 figure5:**
[figure not shown]
Examples of online Facebook and Google AdWords used in recruitment for study.

### Recruitment Tracking

To assess the effectiveness of the different recruitment approaches and reach of each advertisement/link, an advertisement tracking system will be implemented using the online open analytics platform *Piwik* [36]. This method involves adding a unique *campaign* and *keyword* code to the source name as a parameter at the end of each link where the advertisements, banners, and links will be embedded.

### Study Hypothesis

The primary hypothesis is that the active intervention group (OWC with The Toolbox) will exhibit an increase in participant well-being [as measured by the Mental Health Continuum Short Form (MHC-SF) scores] after 4 weeks, in comparison with the control group (OWC without The Toolbox).

### Primary Outcome Measure

The primary outcome is mental health (well-being), assessed using the MHC-SF [37]. This scale consists of 14 questions measuring three areas of well-being, namely, emotional, psychological, and social. The tool diagnoses mental health as flourishing, moderately mentally healthy, and languishing, consistent with the Complete State Model of Health theory. The MHC-SF has been validated with adolescents and adults in the United States, South Africa, and the Netherlands. It has an internal consistency over Cronbach alpha = .80 [38-41]. The test-retest reliability of the MHC-SF over three successive 3-month periods averaged .68, and the 9-month test-retest reliability was .65 [40]. A clinically significant change will be defined as a change in diagnostic outcome (languishing, moderately mentally healthy, and flourishing) between measures before and after the intervention in at least one of the well-being categories (emotional, psychological, and social). We will also consider changes in heuristic trackers as reflective of behavioral change (sleep, mood, energy).

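### The definition of clinically significant change has no direction and is met by any one of three areas, so it counts deterioration as well as improvement and barely registers the planned effect

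*Protocol article*

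**What the plan says.** Primary Outcome Measure introduces the three-state classification as an output of the instrument as a whole: "The tool diagnoses mental health as flourishing, moderately mentally healthy, and languishing". Background likewise describes the three states as "based on symptoms of positive feeling and functioning in life", which takes feeling and functioning together. Primary Outcome Measure then fixes the responder rule: a clinically significant change is "a change in diagnostic outcome (languishing, moderately mentally healthy, and flourishing) between measures before and after the intervention in at least one" of the three areas. No direction is given, and the article does not say how a single area is assigned to one of the three states.

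The stated aim has a direction. The abstract says "Small but clinically significant increases in well-being symptoms are expected to be detected" in the intervention group compared with control, and Study Hypothesis also predicts an increase.

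On stability, Primary Outcome Measure reports "The test-retest reliability of the MHC-SF over three successive 3-month periods averaged .68" and "the 9-month test-retest reliability was .65", with internal consistency above .80. It gives no 4-week value and no value for the separate areas. Statistical Analysis takes the well-being score, not this rule, as the dependent variable of the primary model.

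**The concern.** This is a definition that the article states, not a detail left to a fuller document. It raises three problems.

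- **Direction.** A participant who falls from flourishing to languishing is counted as having a clinically significant change. The rule does not measure the increases that the abstract expects.
- **Three chances.** One crossing in any one area is enough, so random crossings add up.
- **Level of classification.** A diagnosis described for the whole tool is applied to each area without a stated way of doing so.

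This is the article's only definition of clinical significance, and the abstract uses that term for the expected result. As worded, the term would attach to a rate that is high in both arms, mixes benefit with harm, and responds little to a real effect.

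**Working it through.** The article gives no expected proportion meeting the rule, so there is no figure of its own to reproduce. The check asks how often a participant with no true change would meet the rule, and how far the planned effect moves that rate.

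**Inputs from the article.** Retest correlation r = .65 and .68 and internal consistency above .80 (Primary Outcome Measure); 42% flourishing (Background); target difference 0.37, with SDs 0.63 at baseline and 0.81 at follow-up (Sample Size).

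**Inputs assumed.** Central scenarios: languishing 5-16%, correlation between areas 0.5-0.7. Full grid: languishing 5-20% (down to 1% in one check), flourishing 25-50% per area, correlation 0.4-0.8. Errors were taken as either independent or correlated across areas.

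**Model.** For each area, x1 = √r·T + √(1−r)·e1 and x2 = √r·T + √(1−r)·e2 + d, where T is the stable true score and d = 0 for no change. Both visits are cut at Φ⁻¹(p_languishing) and Φ⁻¹(1 − p_flourishing). The rule is met if the category differs in at least one of three areas. Each scenario used at least 400,000 simulated participants.

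**One scenario in full.** Take r = .68, 10% languishing, 42% flourishing, correlation 0.6 (errors included).
- One area changes category in 35.9%, half of those upward (17.9%).
- Three independent areas would give 1 − (1 − 0.359)³ = 1 − 0.263 = 73.7%. With correlation 0.6 the result is about 69%.

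**Share meeting the rule with no true change.**

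| Reliability | Central scenarios | Full grid |
|---|---|---|
| .65 | – | 53-79% |
| .68 | 62-75% | 51-77% |
| .80 | 53-66% | 43-69% |
| .90 | 41-53% | 34-55% |

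Alternatives at r = .68, full grid:
- upward move in at least one area: 26-49%
- any move in one overall diagnosis: 27-41%
- upward move in one overall diagnosis: 13-21%

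**Response to the planned effect.** The target is 0.37/0.81 = 0.46 SD or 0.37/0.63 = 0.59 SD, assumed to shift all three areas equally. In the scenario above with 0.46 SD, the share with an upward move rises from 37% to 55% and the share with a downward move falls from 37% to 17%. The share meeting the written rule stays at about 69%. (Upward and downward shares overlap, because one participant can rise in one area and fall in another.)

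The next table gives the change in percentage points over both effect sizes, with 42% flourishing, languishing 5-15%, correlation 0.5-0.65 and both error structures.

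| Reliability | Rule as written | Upward only, any of three areas |
|---|---|---|
| .65-.68 | −1 to +5 | +17 to +25 |
| .80 | +2 to +10 | +21 to +30 |
| .90 | +9 to +18 | +26 to +38 |

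An upward move on a single score gains 12-17 points at .65-.68.

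**The case against.** **Direction is supplied elsewhere.** The abstract and Study Hypothesis both speak of an increase, so the rule could be read as a threshold for the size of change, with the sign taken from context. On that reading, chance positives at r = .68 fall to 26-49%. This is a fair reading of the intent, but the definition does not say it, and an analyst following the wording would count deteriorations.

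**The reliabilities do not fit the use made of them.** The .68 and .65 are for the whole scale over 3 and 9 months and include true change; the trial lasts 4 weeks. Internal consistency above .80 suggests that pure error could be smaller. The 42% is an overall diagnosis in 13-17-year-olds, and the other shares and correlations are assumed. All of this stands. A reader might infer that most participants with no true change would meet the rule. The documents do not establish that: it holds across the grid at the quoted values, is likely but not certain at 0.80, and is about even or fails at 0.90. Reliability of a single area could also be lower than that of the whole scale, which would raise the rate.

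**Nothing inferential rests on the rule.** This also stands. A reader might infer that the primary test is compromised or that a false benefit would be created. Neither follows: the hypothesis, sample size and primary model all use the MHC-SF score, and with a concurrent randomised control the noise falls on both arms and mainly dilutes the contrast. Nor does the article propose to report a within-arm rate as evidence of benefit.

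**Conclusion.** The point holds as a fault in the responder definition. That the rule lacks direction, allows three chances, and applies a whole-tool diagnosis to each area can be read from the text without any calculation.

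The size depends on assumptions. With assumed category shares and correlations, roughly half to three-quarters of stable participants could meet the rule at the quoted retest values, and about one-third to two-thirds at a reliability of 0.80-0.90. The loss of sensitivity is clearer. At every reliability tried, the written rule responded less to the planned effect than the same rule limited to upward moves, and at .65-.68 it hardly responded at all. This assumes that the effect shifts all three areas equally.

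The consequence is confined to the interpretation of clinical significance. The type I error and power of the primary analysis are untouched. The definition should be corrected, but the trial's main conclusion does not depend on it.

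**What to change.** Define clinically significant improvement as an upward shift in the single overall MHC-SF diagnosis: languishing to either higher state, or moderately mentally healthy to flourishing. Report downward shifts separately as deterioration. Interpret the rate only as a comparison between arms adjusted for baseline category, for example with a logistic or ordinal model. The between-arm comparison is still needed after rewording, because 13-21% of stable participants would shift upward by chance at r = .68.

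The cost is one reworded definition. The same 14 items are used, with no new data and no added burden on participants. The small downside is that the quoted rate of change will be lower.
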